#### Bone density

Quantitative computed tomography (QCT) is used to measure bone mineral density using Discovery MI computed tomography (CT) scanner (GE Healthcare, Waukesha, WI, US) with a solid Mindways QCT Phantom (Mindways Software Inc., Austin, TX, US, model QCT Pro) immediately after the FDG-PET scan [48]. Vertebrae L2 to L4 are scanned in the supine position. Calibration phantom is used to convert Hounsfield Units into bone mineral equivalents in mg · cm^− 3^ using QCT Pro software (Mindways Software Inc., Austin, TX, USA), with which the CT images are analyzed [49].

#### Blood samples

During the visits 1 and 3 (Fig. 1), blood samples are obtained in a fasted state (10 h) in the morning. From the samples complete blood count, glycated hemoglobin (HbA1c), lipid profiles, liver enzymes and C-reactive protein are determined. Before the FDG-PET study (visits 2 and 4 in Fig. 1), fasting state blood samples are collected and stored in a freezer (− 70 °C) for further analyses.

#### Oral glucose tolerance test

A 2-h oral glucose tolerance test (OGTT) is performed after at least a 10-h fast during the visits 1 and 3. (Fig. 1). After ingestion of 250 ml of liquid containing 75 g of glucose (﻿GlucosePro, Comed Oy, Ylöjärvi, Finland), blood samples are collected at baseline, 15, 30, 45, 60, 90, and 120 min during the test to determine glucose, C-peptide, and insulin concentrations in the blood.

#### Muscle and adipose tissue samples

Muscle and adipose tissue biopsies are collected at the end of the PET imaging visit in a post-prandial state. Subcutaneous adipose tissue is collected from the right side of the lower abdomen and the lateral side of the right thigh using open surgical procedure. After the selected skin area is sterilized and local anesthetic (lidocaine supplemented with epinephrine) administered, a small incision is made from which the adipose tissue sample is extracted with a sharp knife and anatomical forceps. Muscle biopsy is collected from the vastus lateralis muscle inferior to trochanter major and anterior to lateral fascia using suction-modified Bergström muscle biopsy technique [50] from the same cut as the femoral adipose tissue sample. Post-intervention tissue samples are collected as near to the locations of the baseline samples as possible, avoiding the scars. One part of the biopsies is flash frozen in liquid nitrogen and stored at freezer (− 70 °C). The other part is put in formalin and subsequently embedded in paraffin. The incisions are closed with absorbable sutures.

#### Faeces and urine samples

Faeces and urine samples are collected at the first PET imaging visit to determine gut microbiota and metabolomics, respectively, midway through the training intervention, and at the last PET imaging visit. The participants fill out a 3–4 day food diary before giving the faeces sample. The samples are stored in a freezer (− 70 °C) prior to a total DNA extraction and further analysis.

Total DNA will be extracted from the fecal material (approx. 100–200 mg) using a commercial DNA extraction Kit following the manufacturer’s instructions. DNA concentration will be measured using Qubit® 2.0 Fluorometer (Life Technology, Carlsbad, CA, US) for further analysis.

DNA libraries will be performed with the amplification of the Specific 16S ribosomal RNA (rRNA) gene region (V3-V4) following Illumina protocols. A multiplexing step will be conducted by the NextEra XT Index Kit (Illumina, San Diego, CA, United States). 16S amplicons will be confirmed and checked with a Bioanalyzer DNA 1000 chip (Agilent Technologies, Santa Clara, CA, United States). Libraries will be sequenced on Illumina platform according to manufacturer instructions. During DNA extraction and PCR amplification, the reagent contamination is controlled and ruled out by using blanks not containing a sample.

Quality-trimmed and filtering will be assessed using DADA2 pipeline. Taxonomic assignment will be conducted using the Silva v132 database. Samples with less than 1000 reads will be removed from the final analysis. Sequences not assigned to Bacteria domain level, also, those sequences classified as cyanobacteria and chloroplasts, likely represent ingested plant material, will be removed from the dataset.

#### Neuropsychological test battery

Neuropsychological function is assessed by an online survey using Gorilla Experiment Builder (gorilla.sc) platform [51]. The survey consists of several tasks that measure working memory (N-back tasks with *N* = 1 and *N* = 2, digit span text entry), memory encoding and retrieval with CERAD Word List Memory task type test, vigilance, simple reaction time, and fluid intelligence with The matrix reasoning item bank (MaRs-IB) [52] which is a modified open-source variant of the Raven’s progressive matrices test. Emotional sensitivity was measured by asking subjects to report their feelings of valence (pleasure-displeasure) and arousal to a set of pleasant, unpleasant and neutral pictures derived from the International Affective Picture system (IAPS) [53, 54]. The survey is performed after the lunch during an afternoon of a PET study day in a quiet room using a standard desktop computer.

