## Methods

### Study design

The CROSSYS study is an exercise training intervention with a single group assignment, and the study is prospectively registered on 5th November 2018 in ClinicalTrials.gov with the identifier NCT03730610. We investigate the effects of exercise training on closely related physiological systems that are central for the regulation of the body metabolism. These include: *i.* tissue-specific insulin-stimulated glucose uptake (insulin sensitivity) in brain, liver, intestine, subcutaneous and visceral adipose tissues, in muscle and myocardium, *ii.* whole-body insulin sensitivity, endogenous glucose production and pancreas function, *iii.* Brain morphology and inflammation, *iv.* cognitive functioning, *v.* ectopic fat masses in and around organs, *vi.* adipocyte size, angiogenesis, inflammation, glucose transporters, adipokines and myokines in femoral muscle and abdominal and femoral subcutaneous fat tissues, *vii.* Metabolomics, *viii*. Comprehensive blood profile, *ix.* glucose tolerance and *x*. microbiota diversity and the associations between microbiota and tissue specific insulin sensitivity especially in the gut-brain axis.

The study flow is illustrated in Fig. 1. The eligibility of the participants is first evaluated in a phone interview, followed by a screening visit to ensure that the inclusion criteria for the twin pair are fulfilled. During the screening visit, participants are thoroughly examined by a medical doctor, including electrocardiography (ECG). Within 1–4 weeks after the screening visit, the twin pairs arrive to baseline measurements, which are described in detail below. Then, both co-twins exercise four times a week for 6 months in their place of residence (Table 1), receiving guidance from a personal trainer once a week. At 3 months, participants take a urine and faeces sample and fill out the food diary. After 6 months, the same measurements as at the baseline are repeated (Fig. 1). Participants are asked to avoid strenuous exercise as well as caffeinated drinks and alcohol 48 h before each study visit. The usage of nicotine-products is not restricted prior to the measurements. Participants are required to fast overnight (at least 10 h) before all the study days except for the study day 1 during the visits 2 and 4 (Fig. 1).

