### Statistical analysis and modelling

#### Power calculation

The sample size calculations are based on liver fat content and VO_2max_ results from the earlier cross-sectional study in twins discordant for physical activity and fitness [56, 57], and on M-value [58]. The data will be analyzed with hierarchical linear mixed model which take into account the correlation between repeated measurements and twins. Model will at least include training as categorical factor and time as within factor. It will be investigated whether there are significant change in mean values over time (training effect) and whether training effect is different between the heavier and the leaner twins.

For the VO_2max_, to test the effectiveness of the intervention, the evaluated sample size is calculated using the mean VO_2max_ value for the less active twins [57]. Standard deviation (SD) between twin pair measurements was 2.8 and correlation between measurements over 0.93. With these assumptions we wanted to evaluate the sample size needed to detect a 5–10% mean difference. Due to high correlation, the sample size needed for a 5% mean difference is 6 twin pairs. For a greater mean difference than 5%, the sample size would be even lower. The corresponding values for liver fat content are 2.1%, SD 1.39, and correlation over 0.98 and due to high correlation, the sample size needed for a 20% mean difference is 22 twin pairs [56]. These values for the whole-body insulin sensitivity are 6.2 mg/kg fat-free mass/min, SD 0.3, and correlation over 0.7, and the sample size needed to detect 30% mean difference is 6 twin pairs [58].

According to these calculations, at least 22 pairs is needed for the study. We are unable to calculate the sample size for all the main parameters due to non-existing twin data. However, we believe that the same schema will hold true in the other main parameters due to the high correlation of twins and small variation within the twin pairs.

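### For the repeated cognitive and picture-rating tests, the mean change called the training effect mixes training with practice or habituation, because everyone trains and everyone is retested

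*Protocol article*

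**What the plan says.** The Study design section of the protocol article describes an "exercise training intervention with a single group assignment" in which "both co-twins exercise four times a week for 6 months in their place of residence". Among the ten systems on which effects of exercise are investigated, the fourth includes "cognitive functioning". On retesting it says: "After 6 months, the same measurements as at the baseline are repeated".

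The Neuropsychological test battery section lists N-back and digit span for working memory, then "memory encoding and retrieval with CERAD Word List Memory task type test, vigilance, simple reaction time, and fluid intelligence". It adds valence and arousal ratings of "a set of pleasant, unpleasant and neutral pictures derived from the International Affective Picture system". It does not mention test versions, alternate lists or a familiarisation session.

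The Power calculation section names two questions for the mixed model. One is whether there is "significant change in mean values over time (training effect", the bracket giving the label. The other is "whether training effect is different between the heavier and the leaner twins". The Statistical analysis section gives the design factors as time, twin and their interaction, with covariates such as adherence added when appropriate. The limitations in the Discussion are diet, adherence and missing data; retest effects are not among them.

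**The concern.** A person who meets N-back, a word-list task or matrix reasoning a second time knows the task and may have a strategy for it. Scores can rise for that reason alone. Ratings of affective pictures may shift through habituation. An FDG uptake value or a spectroscopic fat content cannot be learned in this way, so the problem is more specific than the general weakness of a before-after study.

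If the plan is followed as written, whatever the second sitting adds is reported as an effect of exercise on cognition or emotional sensitivity. An analysis plan written later cannot recover the split, because no one in the study is retested without training.

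Elsewhere the article does state safeguards for before-after comparability: the same gas-exchange device for each pair at both tests, and biopsy sites close to the earlier ones while avoiding scars. It states none for cognition.

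**Working it through.** **1. What the coefficients estimate.** For a twin, write the expected after-minus-before change as T + P + O, where T is training, P is practice or habituation, and O is any other change over 6 months.

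- Time main effect = mean of T + mean of P + mean of O over all twins. No participant has P without T, so the terms cannot be separated.
- Time x twin = (T heavier − T leaner) + (P heavier − P leaner) + (O heavier − O leaner). P drops out if practice is equal in both co-twins.

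Sharing a genome does not help the first contrast, since both twins train and both are retested.

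**2. Number of pairs.** The Participants section invites 54 pairs, expects 25% not to take part or not to be eligible, and another 25% to drop out: 54 × 0.75 × 0.75 = 30.4. This reproduces the stated 30 pairs.

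**3. Size of the effect on the time test.** The documents give no cognitive SD, retest gain or retest correlation, so these are assumptions: retest gain g = 0.1 to 0.3 baseline SD; before-after correlation r = 0.7; within-pair correlation of change c = 0 to 0.5; true training effect zero. The test is two-sided at 0.05, as the plan states.

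- SD of change per twin = √(2(1 − r)) = √0.6 = 0.775.
- SE of the mean change with 30 pairs = 0.775 × √((1 + c)/(2 × 30)): 0.100 at c = 0 and 0.122 at c = 0.5.
- Noncentrality = g/SE. The rejection probability comes from the noncentral t with 29 df.

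| Retest gain g | Noncentrality (c = 0.5 to 0) | Chance of p<0.05 for time |
|---|---|---|
| 0 | 0 | 5% |
| 0.1 SD | 0.82 to 1.00 | 12-16% |
| 0.2 SD | 1.63 to 2.00 | 35-49% |
| 0.3 SD | 2.45 to 3.00 | 66-83% |

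Sensitivity: with r from 0.5 to 0.8, the figure at 0.3 SD runs from 45% to 94%. With 22 pairs, the minimum in the Power calculation section, and r = 0.7, it is 10-13% at 0.1 SD and 52-69% at 0.3 SD.

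**4. Time x twin.** In 20,000 simulated trials (30 pairs, r = 0.7, c = 0), an equal gain of 0.3 SD in both twins gave 4.9% rejections. Gains of 0.2 SD in one twin and 0.4 SD in the other gave about 16%. The interaction is protected only as far as practice is similar in heavier and leaner twins.

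**The case against.** **Item reuse is not documented.** A reader might infer that the same words, matrices and pictures are shown twice. The only support is the general sentence on repeating measurements, which also covers PET, MRI and biopsies. The battery section fits either reading, and an article may leave version details to the full protocol. This objection stands, so item memory is only a conditional part of the point. Task familiarity does not depend on item reuse.

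**This is the open limit of any single-group study.** In part, yes: the design is stated plainly, and parallel versions would not remove task familiarity. But the text calls the mean change the training effect, and its list of limitations omits a cause that is particular to these tests.

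**Adherence may enter the model.** It is listed as a possible covariate. As listed, it is not a time-by-adherence term, and adherence is not randomised, so it would not cleanly separate practice from training.

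**The consequence is limited.** This also stands. A reader might infer that practice pushes results towards the trial's hypothesis, so that the cognitive aim could be declared met without any effect of exercise. The article states no directional cognitive hypothesis and no success criterion, tests are two-sided, and the named primary outcomes are tissue glucose uptake and the M-value. The direction for picture ratings cannot be derived from the documents.

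**Conclusion.** The point holds for the main effect of time in the cognitive and picture-rating outcomes. That contrast cannot be read as a training effect under the stated design and model. This follows from the text and needs no numerical assumption.

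The size does rest on assumptions. With 30 pairs, r = 0.7 and c = 0 to 0.5, retest gains of 0.1 and 0.3 SD raise the chance of a significant time effect from 5% to about 12-16% and 66-83%. A normal approximation that treats the 60 twins as independent gives about 17% and 85%. Those figures are slightly too high, because the planned model is for correlated twins.

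The comparison of heavier and leaner twins is much less affected, given similar practice in both. The primary metabolic outcomes are not touched. This should be corrected, but it does not threaten the trial's main conclusions.

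**What to change.** **For the whole battery, whatever the stage of data collection.** Report the mean change as pre-post change and not as a training effect. Add retest effects to the limitations in the Discussion. Rest exercise-related inference on time x twin, stating that it assumes similar practice in both co-twins and that it tests whether change differs between them, not whether training improves cognition. This costs only wording and a weaker cognitive claim.

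**For pairs not yet tested at baseline.** Use two versions of the word list, the matrix items and the picture set. Randomise the order by pair, give both co-twins the same version at each visit, and add a version term to the model. This reduces item carry-over but does not remove task familiarity, so the reporting change still applies. The cost is a small amount of set-up work in the online platform, including matching the versions, and possible small differences in difficulty, which the randomised order balances on average.

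**For pairs already tested at baseline.** Enrolment began in January 2019, so such pairs are to be expected. Do not move all of them to a new version at follow-up: with a fixed order, version difficulty would be aliased with time. Either keep the version, or randomise by pair which version is given at follow-up.

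The article should also state which versions are used at each visit.

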#### Physical activity questionnaire

Habitual physical activity is assessed using a questionnaire by Baecke et al. [55] before and after the exercise intervention period. It consists of 16 questions divided into three sections: physical activity at work, during leisure time (sport excluded) and during sport. Three indices measuring the level of habitual physical activity are calculated (work, leisure and sport index). The questionnaire is performed as an in-person interview conducted by a researcher during a PET study day.

#### Body composition, maximal exercise capacity and muscular strength

Body composition measurements, a maximal oxygen uptake (VO_2max_) exercise test and tests for muscular strength are performed to each participant before and after the training intervention. The tests are performed at the Paavo Nurmi Centre (Turku, Finland).

Participants’ body composition is measured using a bioimpedance analysis machine (Inbody 720; Biospace Co, Korea). The machine measures participants’ total mass, skeletal muscle mass, body fat mass, body mass index, body fat percentage, and the lean mass balance between left and right arm, left and right leg and the trunk.

VO_2max_ is measured using a stationary bicycle ergometer (Ergoline 800 s; VIASYS Healthcare, Germany). For men, the test starts with 50 W which is increased by 30 W every 2 min until volitional exhaustion. For women, the test starts with 40 W which is increased by 20 W every 2 min until volitional exhaustion. Ventilation and gas exchange (Jaeger Oxycon Pro; VIASYS Healthcare or Vyntus CPX, Vyaire Medical Gmbh, [name], Hoechberg, Germany) are measured during the test. The PRE and POST test for each pair is conducted using the same device. Participants’ blood lactate concentration is measured from capillary samples immediately and 1 min after exhaustion (YSI 2300 Stat Plus; YSI Incorporated Life Sciences, Yellow Springs, OH). The heart rate of the participants is followed continuously with an ECG-machine (CardioSoft GE, CardioSoft V6.51; GE Medical Systems Information Technologies, USA).

Muscle strength is tested using repetition tests for sit-ups, back extensions, and dumbbell overhead press. Maximal grip strength of the dominant hand and indirect test for vertical jump height are also performed. For abdominal muscle strength, participants perform as many repetitions of abdominal crunches as possible in a 30 s time frame. The participants lie on their back in an ab bench with legs fixed into a 90° knee angle, hold hands behind the neck and point elbows forward. Participants’ elbows and knees must touch every repetition. The back strength is measured with a Roman chair with added metal rods that form a 90° angle. Participants perform back extensions with hands behind the neck and elbows pointing directly to the sides as many repetitions as possible in a 30 s time frame. During one repetition participants’ elbows must hit both the upper and the lower metal rods. Arm strength is measured with a standing dumbbell overhead press test. The mass of the dumbbells used during the test are 10 kg for men and 5 kg for women. The aim of the test is to get as many repetitions as possible alternating arms every repetition. Participants are allowed to use only their stronger arm in the end of the test, if a failure in the concentric phase for the weaker arm occurs, in order to conduct as many repetitions as possible. Once the participant has chosen to use only one arm, he or she cannot use the other arm during the test. Maximal grip strength is measured with a computerized digital dynamometer (GOOD STRENGTH dynamometer Metitur Oy, Jyväskylä, Finland). Participants may choose which arm they use for the test. Explosive leg muscle strength is assessed from a vertical counter-movement jump height that is indirectly calculated from the flight time that is recorded by a led-light beam system (OptoJump Next; Microgate, Italy). Participants are instructed to hold their hands at the waist to nullify the effect of the arms during a countermovement-jump. Participants jump 3–5 times and the average of the three best flight times is used to calculate the jump height.

### Statistical analysis and modelling

#### Power calculation

The sample size calculations are based on liver fat content and VO_2max_ results from the earlier cross-sectional study in twins discordant for physical activity and fitness [56, 57], and on M-value [58]. The data will be analyzed with hierarchical linear mixed model which take into account the correlation between repeated measurements and twins. Model will at least include training as categorical factor and time as within factor. It will be investigated whether there are significant change in mean values over time (training effect) and whether training effect is different between the heavier and the leaner twins.

For the VO_2max_, to test the effectiveness of the intervention, the evaluated sample size is calculated using the mean VO_2max_ value for the less active twins [57]. Standard deviation (SD) between twin pair measurements was 2.8 and correlation between measurements over 0.93. With these assumptions we wanted to evaluate the sample size needed to detect a 5–10% mean difference. Due to high correlation, the sample size needed for a 5% mean difference is 6 twin pairs. For a greater mean difference than 5%, the sample size would be even lower. The corresponding values for liver fat content are 2.1%, SD 1.39, and correlation over 0.98 and due to high correlation, the sample size needed for a 20% mean difference is 22 twin pairs [56]. These values for the whole-body insulin sensitivity are 6.2 mg/kg fat-free mass/min, SD 0.3, and correlation over 0.7, and the sample size needed to detect 30% mean difference is 6 twin pairs [58].

According to these calculations, at least 22 pairs is needed for the study. We are unable to calculate the sample size for all the main parameters due to non-existing twin data. However, we believe that the same schema will hold true in the other main parameters due to the high correlation of twins and small variation within the twin pairs.

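### The liver-fat figure of 22 pairs, the sole support for the stated minimum sample size, does not follow from its printed mean, SD, correlation and effect

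*Protocol article*

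**What the plan says.** The Power calculation section has three rows.

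- **VO2max:** "Standard deviation (SD) between twin pair measurements was 2.8 and correlation between measurements over 0.93"; "the sample size needed for a 5% mean difference is 6 twin pairs". The mean is left to the cited study.
- **Liver fat:** "The corresponding values for liver fat content are 2.1%, SD 1.39, and correlation over 0.98", and then "the sample size needed for a 20% mean difference is 22 twin pairs". The text puts this number down to the high correlation.
- **Whole-body insulin sensitivity (M-value):** "These values for the whole-body insulin sensitivity are 6.2 mg/kg fat-free mass/min, SD 0.3, and correlation over 0.7"; "the sample size needed to detect 30% mean difference is 6 twin pairs".

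The section concludes: "According to these calculations, at least 22 pairs is needed for the study". Only the liver-fat row reaches 22, so that row sets the minimum.

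The Statistical analysis section fixes two-sided tests at 0.05. Two effects are to be tested: the change over time, and whether that change differs between the heavier and the leaner twin. The Participants section invites all 54 available pairs and expects 30 to complete.

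**The concern.** The article prints the mean, SD, correlation, percentage difference and resulting number of pairs for liver fat, so the result can be checked. With a correlation of 0.98, paired differences have a very small SD, and a 20% difference should need only a handful of pairs. Either the 22 or one of its inputs is therefore misstated.

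What is at stake is the only stated justification of the sample size. The section also extends the same reasoning to the other main parameters, for which no twin data exist. While the row does not reproduce, a reader cannot tell how much margin 22 or 30 pairs provide. The M-value row has a similar mismatch. It does not set the minimum, but the M-value is a named primary outcome.

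**Working it through.** **Method.** Paired t-test with exact noncentral-t power, two-sided alpha 0.05. Alpha is taken from the Statistical analysis section and assumed to apply to the power calculation. Power is not stated, so 80%, 90%, 95% and 99% are all tried. Where the text says the correlation is over a value, that value is used, because it gives the largest number of pairs.

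SD of a paired difference = SD × √(2(1 − r)); standardised effect d = difference ÷ SD of the difference.

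**Liver fat: attempt to reproduce 22**

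- Difference: 0.20 × 2.1 = 0.42
- SD of the paired difference: 1.39 × √(2 × 0.02) = 1.39 × 0.2 = 0.278
- d = 0.42 ÷ 0.278 = 1.51

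For the contrast between heavier and leaner twins (time × twin), the SD is 0.278 × √2 = 0.393, taking the two twins' changes as independent, so d = 1.07. If 1.39 is already the SD of within-pair differences, d = 0.42 ÷ 1.39 = 0.302.

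| Reading | 80% | 90% | 95% | 99% |
|---|---|---|---|---|
| Paired difference, r = 0.98 | 6 | 7 | 8 | 11 |
| Time × twin, r = 0.98 | 9 | 12 | 14 | 19 |
| 1.39 as SD of differences | 88 | 118 | 145 | 204 |

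The figure of 22 is not reproduced. Covariance adjustment for baseline gives 6 or 7 pairs (80% or 90% power), a log scale 5 or 6, a one-sided test 5 or 6, and an unpaired comparison 172 or 231 per group.

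Power of 22 pairs for the paired difference is above 99.9% when the stated correlation is used. If 1.39 is the SD of differences, it is about 27%, and about 36% with 30 pairs.

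**What would have to change to give 22.** With SD 1.39 and a 20% difference, r would have to be about 0.88 (80% power) or 0.91 (90%). With SD 1.39 and r = 0.98, the difference would have to be about 8.3% (80%) or 9.6% (90%). These values show the size of the mismatch; they do not identify the error.

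**M-value: attempt to reproduce 6**

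- Difference: 0.30 × 6.2 = 1.86
- SD of the paired difference: 0.3 × √(2 × 0.3) = 0.3 × √0.6 = 0.232
- d = 1.86 ÷ 0.232 = 8.0, which needs 3 pairs at any power from 80% to 99%

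Reading 0.3 as the SD of differences also gives 3. A result of 6 pairs would need an SD of about 1.67 (80%) or 1.44 (90%), roughly five times the printed value.

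**VO2max, for comparison.** SD of the difference = 2.8 × √(2 × 0.07) = 1.048. Six pairs at 80% power fits an assumed mean of about 32 to 35, so this row is plausible under the same formula.

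**The case against.** The strongest reply is that nothing in the conduct of the trial depends on 22. Recruitment draws on a fixed pool: 54 × 0.75 × 0.75 = 30.4, hence the 30 expected completers, and 22 only serves as a floor. The text credits the high correlation, which matters only if 1.39 is the SD of the measurements. That is the more natural reading, and it makes 22 generous. The M-value figure of 6 is likewise conservative and far below 22. All of this stands. It limits the consequence, but it does not make the printed figures agree.

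A reader might go further and infer four things that the document does not support:

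- **That the trial is under-powered for liver fat, or its enrolment wrong.** This needs the SD-of-differences reading, which makes the stated correlation redundant. The loose description of the SD in the VO2max row leaves that reading open but does not favour it.
- **That the true correlation is much lower.** The document gives only a value over 0.98 for liver fat.
- **That the M-value SD of 0.3 is really a standard error.** This cannot be verified without the cited source.
- **That the unstated power level and VO2max mean are defects in themselves.** A condensed article may leave these to the full protocol or the cited study, and no power from 80% to 99% rescues the 22.

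**Conclusion.** The liver-fat figure is wrong as written. The printed inputs give 6 to 8 pairs for the paired difference at 80% to 95% power, or 9 to 14 for the time × twin contrast, against 22 stated. On the other reading of the SD they give 88 (80%) or 118 (90%). The mismatch is therefore about threefold too many or at least fourfold too few, depending on what the SD describes. The document does not show whether the SD, the correlation, the percentage or the 22 is at fault.

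This rests on a paired t-test, two-sided 0.05, conventional power, and r taken at its stated lower bound. A higher r would reduce the pairs needed on the readings that use it. The M-value mismatch (3 against 6) is real but secondary, because it cannot affect the stated minimum. The finding is an irreproducible planning figure. It does not show that the trial is too small.

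**What to change.** Correct the Power calculation paragraph:

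1. Say for each row whether the SD is of the measurements or of within-pair differences.
2. Go back to the original calculation and correct either the liver-fat input or the 22 so that they agree, naming the power level used.
3. Check the M-value SD of 0.3 against its source, and correct it or the 6.
4. Restate the sentence on the minimum of 22 pairs with the power that 22 and the expected 30 pairs give under the corrected inputs.

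The cost is one rewritten paragraph, with no change to enrolment, conduct or analysis. If the SD turns out to be that of within-pair differences, the restated power for liver fat will be much lower, and the text would need to say so.
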